| Interventions | 11a | 
Experimental Groups (Intervention):
Participants in the experimental groups will engage in a French kiss, defined as a passionate kiss involving the exchange of salivary fluids through the mutual introduction of tongues into each other's mouths, along with lip contact. Participants will receive instructions to perform this kiss for a duration of 40 seconds. While this duration is arbitrary and will be acknowledged as a limitation in the protocol, no prior studies provide a guideline for the specific duration of this type of kiss.
 
 
○ Setting: The intervention will take place in a private space within the dental clinic of the Universidad Católica de Santiago de Guayaquil. Each cubicle, equipped with a dental chair, will be enclosed with screens to ensure the privacy of participants. After completing the kiss, participants will leave the cubicle to provide an unstimulated saliva sample, which will be analyzed to measure pH.
 
 
Control Group:
Participants in the control group will not kiss but will still be required to bring their partners to ensure comparable conditions. The individual who consumes the acidic beverage will remain in the same cubicle for 40 minutes, providing unstimulated saliva samples every 5 minutes, as is required for the experimental groups. The control participants will remain seated and follow the same sample collection timeline as the intervention groups.
 
Implementation Standards:
 
 
○ The intervention (kissing) will be self-administered by participants. The research team will observe the initiation of the kiss to ensure it begins appropriately and will then start the timer
 
 |

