|  | 11b | 
Criteria for discontinuing or modifying allocated interventions for a given trial participant.
If any participant or couple feels uncomfortable or chooses not to continue with the kiss, they will be allowed to withdraw from the study without any consequences. In such cases, all data previously collected for their intervention will be excluded from the analysis.
                                                                                                                                                                                                                                                                                                                                                                                                                                                                                                                                                                                                                                                                                                                                                                                                                                                                                                                                                                                                                                                                                                                                                                                                                                                                                                                                                                                                                                                                                                                                                                                                                                                                                                                                                                                                                                                                                                                                                                                                                                                                                                                                                                                                                                              |

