|                                                           | 18b | 
To ensure participant retention and maximize data completeness, the following strategies will be implemented:
 
 
1. Clear Communication: Participants will receive detailed explanations of the study procedures and expectations during the informed consent process. This includes emphasizing the importance of completing all saliva sample collections.
 
2. Convenient Scheduling: Appointments will be scheduled at times that are convenient for participants to reduce the likelihood of dropouts.
 
3. Supportive Environment: Participants will have access to a comfortable waiting area during the study to ensure a positive experience.
 
 
Handling Dropouts:
 
 
○ If a participant chooses to withdraw from the study, all data collected from that individual will be permanently deleted from the database. This policy ensures respect for the participant's decision and aligns with the principles of informed consent.
 
○ A log will be maintained to record cases of withdrawal, including the number of participants who drop out and their reasons (if voluntarily disclosed), but no data from these participants will be included in the final analysis.
 
                                                                                                                                                          |

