|                            | 20b | 
Missing data will be managed using the following approach:
 
 
1. Complete-Case Analysis: Only participants with complete data for the primary outcome will be included in the primary analysis.
 
2. Sensitivity Analysis: If more than 10% of the data are missing, sensitivity analyses will be conducted using multiple imputation methods to assess the robustness of the findings.
 
3. Documentation of Missing Data: All instances of missing data will be documented, and the reasons for missingness (if known) will be recorded in a study log.
 
                                                                                                                                                                                                                                                                                                                                                                                                                                                                                                                                                                                                                                                                                                                                                                                                                                                                                                                                                                                                                                                                                                                                                                                                                                                                                                                                                                                                              |

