|                          |    | 
 
• Withdrawal Rights: Participants may request the deletion of their data and the destruction of their samples at any time during the study.
 
 
The approved informed consent form explicitly addresses these provisions, guaranteeing participants' autonomy and adherence to ethical standards.
                                                                                                                                                                                                                                                                                                                                                                                                                                                                                                                                                                                                                                                                                                                                                                                                                                                                                                                                                                                                                                                                                                                                                                                                                                                                                                                                                                                                                                                                                                                                                                                                                                                                                                                                                                                                                                                          |

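### Items 11b and 18b exclude and delete withdrawers' data by default, so who is analysed can depend on a post-randomisation event partly specific to the kissing groups

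*Protocol*

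**What the plan says.** Four items of the protocol bear on this.

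- **Item 11b (discontinuing the intervention).** If a participant or couple "feels uncomfortable or chooses not to continue with the kiss, they will be allowed to withdraw from the study without any consequences". The next sentence sets the consequence: "In such cases, all data previously collected for their intervention will be excluded from the analysis".
- **Item 18b (handling dropouts).** "If a participant chooses to withdraw from the study, all data collected from that individual will be permanently deleted from the database". A log keeps the number of withdrawals and any reasons volunteered, "but no data from these participants will be included in the final analysis". This rule covers all three groups.
- **Item 20b (missing data).** "Only participants with complete data for the primary outcome will be included in the primary analysis". The back-up is conditional: "If more than 10% of the data are missing, sensitivity analyses will be conducted using multiple imputation methods".
- **Item 26b (consent provisions).** "Participants may request the deletion of their data and the destruction of their samples at any time during the study".

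Two further items give the context. Under item 11a, "Participants in the control group will not kiss but will still be required to bring their partners to ensure comparable conditions". Under item 17a, participants do not know their group until the day of the experiment.

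**The concern.** A randomised comparison is protected only while people are analysed in the group to which they were assigned, whatever happens afterwards. Here a post-randomisation event decides who is analysed, and one form of that event, not continuing the kiss, cannot occur in the control group. Because the group is revealed on the day, the decision to leave can be a reaction to it. If those who leave the kissing groups would have recovered more slowly or more quickly than those who stay, the comparison of recovery times is shifted, and adding participants does not remove the shift.

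Two conflicts within the protocol make this harder to repair. Item 18b deletes by default, while item 26b describes deletion as something a participant may ask for. And the one planned missing-data sensitivity analysis would need, for these people, the pH values that item 18b erases. This is a stated rule and not detail left open, so a later analysis plan could not restore the data.

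**Working it through.** **Step 1. What exists at the time of withdrawal.** Item 12 gives the order: baseline sample, beverage, post-drink sample, kiss (or wait), then samples every 5 minutes for 40 minutes.

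| Point of leaving | pH values already held | Effect of item 20b alone | Added effect of items 11b and 18b |
|---|---|---|---|
| At the kiss (kissing groups only) | Baseline, post-drink | No recovery time, so not in the primary analysis | The two values are lost as predictors for imputation |
| During sampling, before neutral pH (any group) | Baseline, post-drink, some later values | Not in the primary analysis | Those values are lost to imputation and to the secondary pH outcomes |
| During sampling, after neutral pH (any group) | As above, with the recovery time observed | Could be counted as complete for the primary outcome | An observed outcome is deleted |

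For the first two rows the complete-case rule already removes the person from the primary analysis. Deletion makes the loss permanent and takes away what imputation could use. In the third row deletion itself removes an outcome.

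**Step 2. Which part is tied to allocation.** Item 18b applies to all groups. The part that only the kissing groups can have is not continuing the kiss, since controls do not kiss (item 11a).

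**Step 3. Does the dropout allowance help?** The plan's own figure reproduces. One-way ANOVA with 3 groups, f = 0.76, alpha 0.05 and noncentrality N·f² has power 0.950 at N = 30 and 0.923 at N = 27, so 30 is the smallest equal-group total reaching 95%. Adding 20% gives 30 × 1.20 = 36, which allows for a loss of 6/36 = 16.7%. That restores numbers only. It is a recruitment allowance across all groups and does not forecast how many kissing couples will withdraw.

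**Step 4. What the rule could do, under assumptions the protocol does not give.** Assume no true effect, 15 per group (the size in items 2b and 10), withdrawal only in the two kissing groups at rate r, and correlation ρ between the tendency to withdraw and recovery time. With c the upper-r point of the standard normal and φ its density, the shift in a kissing-group mean, in SD of recovery time, is −ρ·φ(c)/(1 − r). For r = 0.20, c = 0.842 and φ(c) = 0.280, so the shift is −ρ × 0.280/0.80 = −0.35ρ. Type I error of the three-group ANOVA comes from 4,000 simulated trials per setting; its simulation standard error near 5% is √(0.05 × 0.95/4000), about 0.3 percentage points.

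| r | ρ = 0 | ρ = 0.3 | ρ = 0.5 | ρ = 0.8 |
|---|---|---|---|---|
| 5% | 0; 4.4% | −0.03; 5.2% | −0.05; 5.2% | −0.09; 5.7% |
| 10% | 0; 5.0% | −0.06; 5.4% | −0.10; 5.4% | −0.16; 6.3% |
| 20% | 0; 4.8% | −0.11; 5.4% | −0.18; 7.0% | −0.28; 11.3% |

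(Each cell: mean shift in SD; type I error.) A negative shift makes kissing look faster. If those who withdraw would have recovered sooner, the sign reverses.

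**The case against.** Several points on the other side stand.

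- **The loss need not be one-sided.** A reader might infer that deletion falls on the kissing groups alone, with nothing comparable in control. The documents do not support that. Item 18b covers every withdrawal, and controls can leave during their 40 minutes of sampling. The wording on discomfort in item 11b may also be meant generally; only not continuing the kiss is clearly specific to the kissing groups.
- **Item 11b is permissive.** It allows couples to withdraw and attaches exclusion to that case. It does not clearly say that a couple who cut the kiss short but stay for sampling are excluded. It also orders exclusion only; deletion comes from item 18b.
- **Couples who leave at the kiss have little to delete.** They have two pre-kiss pH values and no outcome, and item 20b would omit them from the primary analysis anyway.
- **Imputation is not made impossible in general.** It remains available for participants who stay but miss samples.
- **The amount may be small.** The intervention is one short kiss between established partners, so few may stop.
- **The consent conflict is not proven.** The consent form is not among the pages reviewed, and item 18b says its policy accords with informed consent. Default deletion and a right to request deletion could coexist.

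These points limit the claim but do not remove it. Exclusion still rests on a post-randomisation event, partly specific to the kissing groups, and deletion still cannot be undone.

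**Conclusion.** The point holds as a fault in the stated rule. The existence of the rule is certain from the text; its effect on the result is not. Any bias has unknown size and direction and is zero if withdrawal is unrelated to recovery. In the illustration it stays below 0.1 SD at 5% withdrawal and reaches 0.28 SD, with type I error of 11.3%, only at 20% withdrawal and a correlation of 0.8. Those figures assume withdrawal in the kissing groups alone, which the documents do not say, so they mark what the rule permits and not what to expect.

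A reader might want to state the bias in minutes of recovery time, using the 20% allowance as the kissing-group loss. The documents support neither the loss nor any gap in recovery time between those who leave and those who stay, so no such figure is given.

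The difference between items 18b and 26b is a matter to reconcile. The right to withdraw and to ask for deletion is not in question.

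**What to change.** 1. **Items 11b and 18b:** keep data collected before withdrawal unless the participant asks for deletion under item 26b. Reconcile the three items with the consent form through the ethics committee.
2. **Item 11b:** state that stopping or declining the kiss is not in itself withdrawal from the study. Such couples remain free to leave. If willing, they are invited to complete the saliva samples and are analysed in their assigned group.
3. **Items 20a and 20b:** add a sensitivity analysis that leaves these couples out. Use the retained pH values in the multiple imputation for those who leave without an outcome.
4. **Reporting:** give withdrawals and requested deletions by group.

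Censoring early leavers at their last sample is not part of this change. Item 20a specifies ANOVA or Kruskal-Wallis, which do not accept censored times, and a couple leaving at the kiss would be censored at about time zero. It becomes relevant only if the primary analysis is changed to one that accepts censored times.

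**Cost:** an ethics amendment and a consent-form check, with new consent wording if the form promises automatic deletion. Including couples who did not complete the kiss slightly dilutes the estimated effect. The sample size does not change. Item 2b lists the trial as not yet recruiting, so the change is cheapest before the first couple is enrolled.

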|                          | 6b | 
Explanation for Choice of Comparators
 
The study includes the following groups for comparison:
 
 
1. Control Group: Participants who will not engage in the kissing intervention. This group serves as a baseline for evaluating the natural recovery process of salivary pH after consuming acidic beverages.
 
2. Experimental Group 1: One partner consumes the acidic beverage, and the couple engages in a 2-minute kiss. This allows evaluation of the effect of kissing when only one partner has an acidic pH alteration.
 
3. Experimental Group 2: Both partners consume the acidic beverage before engaging in the 2-minute kiss. This setup examines whether mutual exposure to acidic conditions influences the efficacy of kissing in restoring salivary pH.
 
 
Justification for Comparators:
 
These groups were chosen to isolate the effects of kissing on salivary pH recovery and to assess the variability in outcomes when both partners have altered pH versus only one. The inclusion of a control group ensures that
                                                                                                                                                                                                                                                                                                                                                                                                                                                                                                                                                                                                                                                                                                                                                                                                            |

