| Trial design                                              | 8  | 
The study will be a randomized controlled trial with parallel groups. Participants will be randomly assigned to one of three groups:
 
 
○ Control group: Participants who do not kiss after consuming an acidic beverage.
 
○ Experimental group 1: One member of the couple consumes an acidic beverage, and both partners kiss for 40 seconds.
 
○ Experimental group 2: Both members of the couple consume an acidic beverage and kiss for 40 seconds.
 
 
The results will be used to evaluate whether the act of kissing restores salivary pH more quickly than the time it takes for the body to do so physiologically. This design allows for clear comparisons of the effects of the different conditions, with an appropriate control group.
                                                                                                                                                                                                                                                                                                                                               |
| Methods: Participants, interventions, and outcomes |    |                                                                                                                                                                                                                                                                                                                                                                                                                                                                                                                                                                                                                                                                                                                                                                                                                                                                                                                                                                                                                                                                                                                                                                                                        |

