| Sample size          | 14 | 
The sample size calculation was conducted using the G*Power statistical software (version 3.1.9.7, Fran Faul, Universität Kiel, Germany). The calculation was based on data obtained from the pilot study titled "Comparison of Salivary pH Changes after Consumption of Two Sweetened Malaysian Local Drinks among Individuals with Low Caries Experience: A Pilot Study". This study measured salivary pH changes after consuming acidic beverages and provided the necessary statistical parameters for sample size estimation.
 
Specifically, the following values from the pilot study were used:
 
 
Control group (mineral water): mean = 7.10, SD = 0.18.
 
Experimental group (local drink): mean = 6.86, SD = 0.18.
 
 
To calculate the effect size (<math>f</math>) for ANOVA, the means and standard deviations were combined using the formula:
 $n = \frac{(2 * (Z\beta + Z\alpha)^2 * \sigma^2)}{\Delta^2}$ 
Given the mean difference (7.10 - 6.86 = 0.24) and pooled SD of 0.18, <math>d=1.33d=1.33d=1.33</math>. Dividing by the square root of the number of groups (<math>k=3</math>), the resulting effect size was <math>f=0.76</math>, which is considered a large effect size.
 
The following input parameters were used in G*Power:
 
 
Effect size (<math>f</math>): 0.76 (large effect size based on observed data).
 
Alpha error probability (<math>\alpha</math>): 0.05.
 
Power (1-<math>\beta</math>): 0.95.
 
Number of groups: 3.
 
 
The output indicated that a total sample size of 30 participants is required to achieve a power of 95%, with 10 participants per group. To account for potential dropouts, an additional 20% will be recruited, resulting in a total of 36 participants (12 per group).
 
This effect size and resulting sample size are justified based on the observed differences in the pilot study, which measured salivary pH using similar methods (pH meter, unstimulated saliva samples in test tubes) and reported statistically significant differences between groups. Using this approach ensures that the sample size is both statistically adequate and logistically feasible for this study.
 |

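### The 95% power in item 14 comes from mineral water versus a sweetened drink on a pH level, so it does not apply to kiss versus no kiss on recovery time

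*Protocol*

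**What the plan says.** Protocol item 14 (Sample size) takes its parameters from a pilot study of salivary pH after two sweetened drinks. The two inputs are "Control group (mineral water): mean = 7.10, SD = 0.18" and "Experimental group (local drink): mean = 6.86, SD = 0.18". The effect size follows from them: "Given the mean difference (7.10 - 6.86 = 0.24) and pooled SD of 0.18", hence d = 1.33. This is divided by the square root of 3 and entered as f = 0.76, with three groups and alpha 0.05. The output is a total of 30, which according to item 14 "is required to achieve a power of 95%, with 10 participants per group". A further 20% brings this to 36. Item 14 then says that the differences seen in the pilot study justify the effect size and the sample size.

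The trial's own arms are different. Item 8 (Trial design) defines the control as "Participants who do not kiss after consuming an acidic beverage", and item 6b says of it: "This group serves as a baseline for evaluating the natural recovery process of salivary pH after consuming acidic beverages". Item 11a agrees that control participants drink the acidic beverage and do not kiss. In experimental groups 1 and 2, one or both partners drink it and the couple then kisses. Items 12 and 20a set the primary outcome as the time for salivary pH to return to neutral and compare mean recovery times across the three groups by one-way ANOVA.

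**The concern.** A power statement holds only for the contrast and endpoint on which its effect size is defined. Here the effect size is that of a drink against water. The trial randomises kissing, with acid exposure in every arm. The labels in item 14 hide this. What it calls control is a water group that the trial does not have, and on those figures the condition nearest the trial's no-kiss control is the 6.86 group, which item 14 calls experimental.

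No section gives an expected kissing effect or argues that the water-versus-drink difference can stand in for one. Item 6a says that no research has yet evaluated kissing and salivary pH recovery, so the cited study cannot supply the figure. If the 95% stays in the protocol, a null result could be credited with a sensitivity that was never shown.

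**Working it through.** **Inputs (item 14).** Means 7.10 and 6.86, SD 0.18, alpha 0.05, three equal groups, f = d/√3. The recruitment sizes considered are N = 30 and 36 (item 14) and N = 45, which is 15 per group (items 2b and 10).

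**Step 1: reproduce the plan.** d = 0.24/0.18 = 1.333 and d/√3 = 0.770, which item 14 gives as 0.76. Power is that of the one-way ANOVA F test, from the noncentral F distribution with 2 and N − 3 degrees of freedom and noncentrality N·f². With f = 0.76 and N = 30, the noncentrality is 30 × 0.5776 = 17.3 and power is 95.0%. N = 30 is also the smallest total that reaches 95%. Adding 20% gives 36. The stated figures therefore reproduce for the inputs entered.

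**Step 2: set the contrasts side by side.**

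| | Item 14 | Trial (items 6b, 8, 11a, 12, 20a) |
|---|---|---|
| Reference group | mineral water | acidic drink, no kiss |
| Comparison group | sweetened drink | acidic drink (one or both partners) plus kiss |
| What differs | the drink | the kiss |
| Variable | pH level | time to pH 7 |

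No arm is given water, and the source study concerns drinks, not kissing. Neither the contrast nor the variable matches.

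**Step 3: what the arithmetic supports.** Because f is standardised, the calculation shows only that 95% power needs f of about 0.76 at 10 per group, 0.686 at 12 and 0.608 at 15. Nothing in the protocol says that kissing produces an f of that size on recovery time.

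**Step 4: illustration on the plan's own pH scale.** Suppose that kissing reverses a share s of the 0.24. Then d = s × 0.24/0.18, f = d/√3 and f² = 0.593·s². The share is an assumption, shown as a range.

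| Share reversed | pH difference | Power, N = 30 | N = 36 | N = 45 |
|---|---|---|---|---|
| 100% | 0.24 | 95.5% | 98% | 99.6% |
| 75% | 0.18 | 77% | 85% | 93% |
| 50% | 0.12 | 41% | 49% | 60% |
| 25% | 0.06 | 13% | 15% | 18% |

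For example, s = 0.5 at N = 30 gives noncentrality 30 × 0.593 × 0.25 = 4.4 and power 41%. Scaling from the rounded 0.76 instead gives 76%, 40% and 13% at N = 30. The plan's f rule is kept throughout so that the table isolates the choice of contrast. Whether d/√3 is the right conversion is a separate question, and correcting it would leave the mismatch in place.

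**The case against.** The strongest defence is that some surrogate was unavoidable, since by item 6a no kissing study existed, and that item 14 discloses its source openly. Item 7 asks whether kissing can neutralise acidic saliva, so sizing for full restoration is arguably consistent with the aim. This explains the choice but does not rescue the statement. The protocol does not make that argument, and it presents the water-versus-drink difference as justification rather than as an assumption.

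Three limits on the criticism stand.

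- A reader might infer that 0.24 is the most that kissing could achieve. The documents do not support this. The figure comes from another study's drink, and the trial's beverage is described only as acidic, with no pH or volume. Its deficit may be larger or smaller. If it were 0.48 (assumed, same SD), reversing half would again be 0.24, and on the plan's rule power at N = 30 would be 95%.
- A reader might take the 77%, 41% and 13% as the power of the primary analysis. They are not. They concern a pH level, which is a secondary outcome, and the protocol gives no mean or SD for recovery time.
- The loss depends on the recruitment target. At N = 45 and a 75% share, power on the plan's rule is still 93%.

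Nor does any section say that a null result will be read as showing that kissing does not help. That is a risk, not a stated plan.

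**Conclusion.** The point holds. Item 14's 95% power is for a contrast that the trial does not test and on a variable that is not its primary outcome, so it cannot be claimed for kiss versus no kiss. This follows from the protocol's text and needs no assumption.

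The size can only be illustrated. On the plan's own pH figures and f rule, the 95% at N = 30 requires complete reversal of the difference seen in the cited study. Power falls to about 77%, 41% and 13% at 75%, 50% and 25% reversal, or 93%, 60% and 18% at N = 45. These figures assume SD 0.18, independent units and the stated shares.

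One might go further and say that the trial is underpowered, or name the correct sample size. The documents support neither, because they give no kissing effect and no variability of recovery time. The fault lies in the justification and the stated power. Type I error and the estimates are unaffected.

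**What to change.** In item 14:

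- Withdraw the statements that the pilot study's differences justify the effect size and that the trial achieves 95% power.
- State an explicitly assumed kiss-versus-no-kiss difference after the acidic drink, on recovery time, with an assumed SD. Label both as assumptions.
- Reconcile the recruitment target. Item 14 says 12 participants per group; items 2b and 10 say 15 couples per group. Then report the power that the reconciled number delivers over a range of effects.
- If the cited pH figures are kept, mark them as illustrative and do not call 0.24 an upper bound for this trial's beverage.
- Add that a null result would not exclude a partial effect of kissing.

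The cost is a less favourable stated power and a rewritten item. No extra participants or procedures are needed.
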